## Abstract

Background: Over recent years, the Middle East, and especially Saudi Arabia, has faced multiple changes, including structural-demographic and economic shifts. This has led to massive changes in the population’s lifestyle, including more unhealthy diets and increases in physical inactivity. As a result, accelerating rates of chronic diseases, including type 2 diabetes mellitus (T2DM) are a major public health concern. Current diabetes care in Saudi Arabia focuses on increasing the awareness of patients through various approaches, mainly based on health education, which is found to be suboptimal and ineffective for improving long-term outcomes. This study aims to assess the feasibility and acceptability of using a client-centred approach called health coaching that supports, enables, and engages T2DM patients to take the central role of controlling their own conditions by developing new crucial skills. Methods: A mixed methods randomised controlled feasibility study of health coaching will be used. Participants (n = 30) are adults with T2DM with poorly controlled diabetes (A1C ≥7) who can read and write in Arabic. Eligible participants are randomly allocated to either an intervention or control group for 12 weeks. COM-B model and Behaviour Change Technique Taxonomy version 1 (BCTTv1) guide the intervention curriculum. Predetermined progression criteria will be used to determine whether to proceed to a larger trial or not. Outcomes will be measured at baseline and 3 months. The study’s primary aim is to assess the process of eligibility, recruitment, retention and completion rates, acceptability and suitability of intervention and the time to complete each procedure. The preliminary efficacy of health coaching is the secondary outcome that includes different measurements, such as HbA1c, blood pressure, body mass index (BMI), waist circumference, weight, patients’ self-efficacy, and diabetes self-management. Discussion: This is the first study to explore the feasibility, acceptability, and preliminary efficacy of health coaching that used the Capability, Opportunity, Motivation, Behaviour (COM-B) model and BCTTv1 as guidance to develop the intervention for adults with T2DM in Saudi Arabia. The findings of this study will be used to inform the larger RCT trial if it is shown to be feasible and acceptable.

## 1. Background

Type 2 diabetes mellitus (T2DM) is a widespread chronic disease that poses a real worldwide health threat that is becoming a significant public health concern. T2DM is profoundly impacted by an excess body mass index (BMI) and physical inactivity [1]. Diabetes contributes to lead patients developing severe complications such as heart and stroke disorders, eye problems and complications with hearing, kidney failure, nerve injury, amputations, oral issues, and foot problem [2]. Adults with diabetes are two or three times more likely to develop heart problems and strokes [3]. In addition, there are other negative impacts of diabetes on social life, economic status, and health care services. Since diabetes is a preventable disease, which is strongly related to and affected by lifestyle, self-management is an optimal way to effectively manage it [4].

Worldwide, and especially in Saudi Arabia (SA), the prevalence of T2DM is growing at an alarming pace. According to a WHO report (2017), SA has the second highest rate of T2DM and is ranked the seventh highest in the globe. Additionally, the prevalence rate of T2DM has increased tenfold in the past three decades in SA. About 89% to 97% of all Saudi patients with diabetes are diagnosed with T2DM [5]. About seven million people suffer from T2DM in Saudi Arabia and three million are pre-diabetic. T2DM affects approximately 30% of the Saudi population and this increases with age [6]. The prevalence of T2DM is higher among women than men and with higher BMI individuals [6]. Moreover, it is more than likely that the burden of this chronic disease will only increase owing to factors such as an increased rate of obesity, an ageing population, changing lifestyles and poor diet [7]. The widespread increase in sedentary behaviour and physical inactivity among Saudis contributed to increasing the prevalence of T2DM [8] In SA the high rate of T2DM is associated with the high prevalence of obesity as a result of the fast urbanisation that led to adopting modern western dietary habits such as fast-food and increasing the level of physical inactivity [9].

The healthcare system in SA is still trying to address the alarming challenge of T2DM through several national programs and initiatives, but the outcome is still suboptimal. In SA, several studies have provided evidence that T2DM is not managed effectively [10]. While the current attempts are heavily reliant on awareness-raising campaigns, T2DM patients are still struggling to adopt a healthy diet and lifestyle to manage their conditions effectively. Adopting a healthy diet and lifestyle is an essential element of effective self-management of diabetes [11]. It is noteworthy that lifestyle interventions seem to be at least as effective as medications [12].

Diabetes education-based programs have not always been entirely adequate in bringing about the desired change. Many studies make it clear that awareness alone does not contribute to better self-management practices [13]. The responsibility of controlling T2DM is largely dependent on individual behaviour. T2DM patients are the key players to address this issue, so they need enough time to address their needs to improve their self-management skills. Healthcare providers often do not have adequate time for a face-to-face discussion with patients since regular visits at primary care clinics are usually restricted to 10 to 15 min, which leads to patients feeling negative, overwhelmed, and frustrated. Cost-effective interventions are needed to bridge the gap by listening to patients and helping them to overcome potential barriers. Developing a patient’s self-management skills is crucial to delay or reducing the risk of T2DM. The occurrence of the chronic conditions associated with T2DM can be remarkably diminished or delayed—by 75% or more—with the help of healthier lifestyle behaviour choices made by patients [14]. Self-management interventions are needed that enable patients to control and manage T2DM [15] consistent with the current diabetes treatment philosophy that promotes patient-centred approaches [16].

There have been recent attempts to improve diabetes care in SA with T2DM through diabetes self-management programs. These programs are very uncommon and not gaining widespread adoption [17]. Most lifestyle interventions still rely on education as the core element to improve patients’ self-care. The impact of diabetes education programs is suboptimal [17]. However, most studies have emphasised the significant need to shift the current attention toward employing new approaches that help patients to develop self-management skills. A recent systematic review, conducted on gulf cooperation council countries, included studies in T2DM self-management between 1996 and 2015 and found that none of the studies employed the skills needed to improve patients’ self-management capability, such as problem-solving skills [5]. Moreover, none of the studies has employed a patient-centred approach to work with a patient as an ally rather than an educator. Client-centred interventions that are tailored to the patient’s needs are more likely to bring about desired outcomes [18].

Health coaching is a client-centred approach that is derived from different disciplines and behaviour change theories. It has become an emerging trend in the literature and is gaining widespread acceptance in the health promotion fields but this one-on-one type of tailored intervention has not yet been used in Saudi healthcare systems. Different studies have revealed that health coaching as an intervention centred on patients’ values may provide added benefits to traditional T2DM education programmes [19]. It can be a highly effective and financially viable model when it focuses on improving patients’ self-efficacy and important skills, including goal-setting, and problem-solving [20]. Health coaching has been applied in multiple different contexts and showed as an effective tool to improve diabetes self-management [21,22].

However, recent systemic reviews of randomised controlled trials utilising health coaching have reported mixed results, with some reporting that health coaching is effective, while others claim it is ineffective [21,22]. One of the explanations for the inconsistent reported findings across different studies is the lack of agreement on the active ingredients and content of effective health coaching interventions.

There is currently no consensus in the literature on designing an effective health coaching intervention, including the selection of a suitable theoretical basis and active ingredients, or behaviour change techniques [22]. In the absence of such consensus, there is uncertainty towards which coaching methods are more appropriate and effective to use including intervention content as well as the duration, length, and mode of delivery of sessions, particularly when applying health coaching in a new setting [23]. A lack of guidance, ineffective methods used to develop interventions, inappropriately selected intervention components and variation in the reporting of outcomes have been suggested to contribute to the mixed effectiveness of health coaching interventions [24,25,26]. Furthermore, health coaching interventions that have been developed and have succeeded in Western or other contexts may not be effective for people in different contexts such as SA. Consequently, such interventions may require adaptation and modification to make them more feasible, acceptable, and suitable in the context of Saudi society.

A feasibility study is highly recommended prior to a full-scale trial to test potential uncertainties, especially when a complex intervention is to be applied in a new context [27]. Feasibility studies help to explore specific issues such as study protocol, context-specific relevance, practicality, and the possibility of efficacy [27,28]. In addition, feasibility studies help examine the procedures’ acceptability, assess the recruitment and retention process, and determine the appropriate sample size for a future full-scale trial [27].

To the best of our knowledge, none of the previous health coaching programs have used the BCW model and BCTs taxonomy as a guide to build the intervention content systematically in order to analyse and achieve planned outcomes. This is aside from the fact the application of diabetes self-management studies within the Saudi context is very uncommon and often focuses on providing health education [17]. Moreover, none of the self-management interventions have engaged stakeholders during the intervention development process, so the interventions may have failed to bring about the change and address the difficulties patients encounter in managing their diabetes [17].

As a result, the future full-scale intervention would be effectively refined and/or inactive ingredients replaced with other appropriate BCTs. Careful selection of theoretical framework and BCTs prior to the intervention being conducted is crucial and widely recommended [29].

### 1.1. Study Aims

The present feasibility study aims to determine whether the health coaching intervention for type 2 diabetes is feasible and acceptable to improve self-management and reduce HbA1C to inform a full-scale RCT trial in SA. The objectives of the study are categorised into the process evaluation objectives (primary) and outcome (secondary) objectives. The process evaluation objectives are related to the implementation phase and mainly focus on the feasibility of processes and procedures of the study. The outcome objectives are related to the efficacy of the intervention.

#### 1.1.1. Primary Objective: (Study Feasibility-Process Evaluation-Objectives)

To assess the feasibility of conducting a future definitive study to evaluate the effectiveness of using an adapted health coaching intervention in the Saudi context by:Assessing recruitment, and retention rates, and estimating the effect size;Assessing the implementation process, including data collection procedures;Assessing and determining the sample size for the larger-scale trial using the findings of this feasibility study;Exploring the acceptability and suitability of intervention through participants’ perceptions of, and experiences with, the health coaching intervention.

#### 1.1.2. Secondary Objective: (Outcome Objectives)

To assess the preliminary efficacy of health coaching to improve diabetes self-management and reduce HbA1C by evaluating its influence on participants’ behaviours and their self-management ability compared to usual diabetes care by:

HbA1c and other variables will be assessed pre- and post-intervention at baseline and at 3 months. The intervention’s clinical goal for T2DM self-management is an HbA1c level of <7.0%. Other variables will also be assessed; namely, glycosylated haemoglobin (HbA1C), blood pressure, body mass index (BMI), waist circumference, weight, patients’ self-efficacy, and diabetes self-management.

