### 2.7. Sample Size

To the best of our knowledge, there was no previous health coaching RCT feasibility study in the field to use as a reference for the sample size. Thus, this study seeks to recruit at least 9% (n = 30) of the sample size required to carry out a full trial [34], with a minimum of 12 participants in each group [35]. Participants will be randomly allocated to either the coaching group (n = 15) or the control group (n = 15).

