#### 2.8.2. Intervention Procedure

Three trained and qualified health coaches will deliver the coaching sessions. They all will receive training on the intervention curriculum (see Table 2). Additionally, they will be monitored by the researchers throughout the period of delivery of the intervention. The intervention consists of 6 sessions that will be delivered biweekly via face-to-face meetings and telephone coaching over a 3-month period. Intervention group participants will be contacted fortnightly and coached using a combination of different methods; in person, by phone, and by smartphone (e.g., secure messaging such as WhatsApp) while the control group participants only receive the usual care for participants with T2DM with includes general lifestyle advice. Face-to-face coaching is only conducted at baseline and in the third month of the intervention for 30–45 min coaching sessions. In addition, 10–15 min telephone coaching will be delivered for the other four sessions (see Figure 1). 

The health coach works as an ally to enable participants to effectively engage in their self-care needs and address potential self-management barriers. They will be provided with different tools, including a patients’ progress tracker, coach notes log and a coaching log to help them run each coaching session. Participants will be given the opportunity to learn and practice significant skills to help them reach target goals through action plans they set for themselves for better self-care [43]. Table 2 illustrates the operationalised protocol and phases of session delivery

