#### 2.8.3. Usual Care (Control Group)

Control group participants will receive only the usual care. Standard care includes providing written information on diabetes and brochures for raising awareness, including the benefits of modifying their health behaviours. Generally, T2DM patients have regularly scheduled visits to check diabetes management by endocrine specialists. The visit’s main purpose is to check whether the patient’s medications need to be replaced, increased, or continue with the same prescription.

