#### 2.9.2. Secondary Outcome Measures

The secondary outcomes (preliminary efficacy) comprise anthropometric, clinical, and psychological variables selected as of the standard measures for monitoring and prevention of complications in diabetes [44]. These variables will be assessed twice at the intervention, at baseline and after 3 months for HbA1C, blood pressure, body mass index (BMI), weight and waist circumference. Change in outcomes post-intervention will help to determine if the intervention is feasible, acceptable, and effective. Table 3 provides the timeline for the assessment of the variables.

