## 3. Data Analysis

### 3.1. Quantitative Data

The feasibility and acceptability of the study’s findings will be evaluated in relation to the quantitative data using descriptive analysis. The descriptive analysis covers different aspects as the following:Screening, recruitment process, retention and adherence (coaching sessions) rates will be calculated and presented as proportionsLength of time to recruit the target sampleDuration of time needed to complete the assessmentsPercentage of completed interventions sessionsAverage time needed to complete each sessionDescription of participants interaction during coaching sessions (frequent BCTs used, interactions with coaches)Acceptability and suitability of intervention through participants’ perceptions of, and experiences with, the health coaching intervention (Satisfaction Questionnaire)Additionally, other outcome measures such as diabetes self-management and patient self-efficacy will be evaluated at baseline and endpoint to investigate changes in participants’ behaviours compared to another groupPreliminary effects of the interventionRegarding the evaluation of the preliminary efficacy of the intervention, secondary variables will be described by means and S.Ds, investigated pre- and post-intervention to measure changes in the outcomes; glycosylated haemoglobin (HbA1C), blood pressure, body mass index (BMI), waist circumference, weight, patients’ self-efficacy, and diabetes self-managementCorrelations will be performed between:The number of completed coaching sessions and A1c, BP, BMI, WC body weight at 3 monthsThe number of completed coaching sessions and self-efficacy and diabetes self-management scales at 3 months

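### The session–outcome correlations in section 3.1 use the 3-month value without the baseline value, so they can create or hide an apparent dose effect if attendance is related to starting level

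*Protocol article*

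**What the plan says.** The schedule gives two measurements of every outcome. Section 1.1.2 states "HbA1c and other variables will be assessed pre- and post-intervention at baseline and at 3 months", and its list covers the clinical measures and both scales. Section 2.9.2 repeats this for the clinical measures, "at baseline and after 3 months for HbA1C, blood pressure, body mass index (BMI), weight and waist circumference". Section 3.1 repeats it for the scales: "diabetes self-management and patient self-efficacy will be evaluated at baseline and endpoint to investigate changes in participants’ behaviours".

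Section 3.1 then describes two uses of these data. For preliminary efficacy, the secondary variables are summarised by means and SDs and "investigated pre- and post-intervention to measure changes in the outcomes". Separately, it lists correlations between the count of completed sessions and (a) HbA1c, blood pressure, BMI, waist and weight, and (b) the self-efficacy and self-management scales. Both are placed at the 3-month assessment. Neither names a baseline value, a change score or an adjustment.

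On exposure, section 2.8.2 says "The intervention consists of 6 sessions that will be delivered biweekly via face-to-face meetings and telephone coaching over a 3-month period". Section 2.7 allocates 15 participants to each arm, "with a minimum of 12 participants in each group".

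**The concern.** Randomisation decides who is offered coaching. It does not decide how many of the six sessions a coached participant attends. People who start better controlled, lighter or more confident may attend more, and people who start worse may attend more because they feel the need. In either case attendance is tied to the starting value. Over 12 weeks the starting value carries over in part to the 3-month value, so a correlation of sessions with the 3-month value inherits that tie even when sessions do nothing.

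What is at stake is the interpretation of a within-arm dose signal. The study is meant to inform and refine a larger trial. A correlation that partly reflects who started where could be read as evidence for or against more sessions. The baseline values needed to remove this component are already being collected.

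**Working it through.** **Plan's own figure.** There is none to reproduce. The article gives no expected correlation, SD, significance level or attendance distribution for this analysis. The sizes below rest on assumed inputs.

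**Inputs from the article.** Sessions range from 0 to 6 (section 2.8.2). There are 15 coached participants, with 12 as the stated minimum per group (section 2.7). The outcome is the 3-month value (section 3.1).

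**Assumed inputs.** rho is the correlation of the baseline with the 3-month value. r_ab is the correlation of attendance with the baseline value.

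**Step 1: expected correlation with no effect of sessions.** Standardise the outcome and write the 3-month value as rho × baseline + noise, with the noise unrelated to attendance. Then corr(sessions, 3-month value) = rho × r_ab.

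- 0.5 × −0.2 = −0.10
- 0.7 × −0.4 = −0.28
- 0.8 × −0.4 = −0.32
- any rho × 0 = 0
- 0.7 × +0.4 = +0.28

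For HbA1c, where lower is better, a negative value looks like a benefit of attending more. A positive value would offset, and so hide, a real benefit. On a scale where a higher score is better, the two readings swap.

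**Step 2: precision at n = 15.** The critical value is |r| = t/√(n − 2 + t²). With t = 2.160 on 13 df this is 2.160/√(13 + 4.666) = 0.514. At n = 12 it is 0.576. For r = −0.28 at n = 15, Fisher's z is −0.288 with standard error 1/√12 = 0.289. The 95% interval in z is −0.853 to 0.278, that is, r from −0.69 to 0.27.

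**Step 3: simulation with no coaching effect.** There were 40,000 trials per setting. Attendance was 0 to 6 sessions skewed towards high attendance, and the test was two-sided at a nominal 5%. The article states no test for these correlations, so the rejection rates only give a sense of scale. Results for n = 15:

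| r_ab | rho | 3-month value: mean r | rejected | change score: mean r | rejected | partial r given baseline: rejected |
|---|---|---|---|---|---|---|
| −0.3 | 0.5 | −0.13 | 7.6% | +0.13 | 7.7% | 5.1% |
| −0.3 | 0.7 | −0.19 | 10.2% | +0.10 | 6.3% | 4.8% |
| −0.3 | 0.9 | −0.24 | 13.7% | +0.06 | 5.5% | 4.9% |
| −0.5 | 0.5 | −0.22 | 12.7% | +0.22 | 12.7% | 5.1% |
| −0.5 | 0.7 | −0.31 | 20.7% | +0.17 | 9.4% | 4.9% |
| −0.5 | 0.9 | −0.40 | 33.3% | +0.10 | 6.2% | 4.9% |

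The simulated means lie a little below rho × r_ab in size, as expected when attendance is cut into whole sessions. With r_ab = 0 the mean r is 0 and rejection is about 5% for every method. With n = 12 and r_ab of −0.3 or −0.5, rejection for the 3-month value runs from 6.9% to 26.1%.

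**Step 4: choice of repair.** The partial correlation given baseline averages 0.00 and rejects 4.8% to 5.3% across all settings at both sample sizes. Change scores do not do as well. With equal SDs at the two visits, corr(sessions, change) = −r_ab × √((1 − rho)/2). This has the opposite sign and is as large as the original bias at rho = 0.5: for r_ab = −0.5, −(−0.5) × √0.25 = +0.25 against −0.25. Conditioning on baseline is the cleaner repair.

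**The case against.** The strongest reply has four parts.

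*The wording may be shorthand.* A condensed article may name the 3-month assessment as the time point and leave open whether the level, the change or an adjusted value is used; the item just before speaks of changes. That is possible, but the literal specification is the 3-month value. Change is attached only to the descriptive summary. A clarifying sentence is needed on either reading.

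*The bias is conditional.* Nothing in the article shows that attendance depends on starting level. This stands. A reader might infer that the planned correlations will show a dose effect that does not exist, but the documents support only that they can. The bias is zero if the two are unrelated and masks an effect if the link runs the other way. Even when present, it carries over only the fraction rho of the starting difference.

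*The analysis is weak with or without adjustment.* At n = 15 the assumed spurious values of −0.10 to −0.32 lie well short of 0.51. This also stands, and it is a reason for reporting an interval. It is not a reason to keep an avoidable bias.

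*Nothing is decided on it.* The correlations sit under descriptive analysis of secondary outcomes. Table 4 judges screening, recruitment, retention and adherence. This stands and limits the priority.

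Two stronger readings should be set aside. A reader might infer that controls will be pooled in as having zero sessions, which would turn the correlation into the between-arm contrast. No section says so: sessions exist only in the coaching arm, and "Control group participants will receive only the usual care". A reader might also take these correlations as the plan's only quantitative link between coaching and outcome. They are not, because sections 1.1.2 and 3.1 also compare the randomised groups.

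**Conclusion.** The point holds in conditional form. Section 3.1 specifies correlations of attendance with 3-month outcomes and leaves out baseline values that the trial collects for every one of them. If attendance is related to starting level, the correlation partly carries over baseline differences and can create or conceal a within-arm dose effect.

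With no true effect the expected size is rho × r_ab: −0.10 to −0.32 for assumed rho of 0.5 to 0.8 and r_ab of −0.2 to −0.4, zero for r_ab = 0, and of opposite sign for positive r_ab. The article supplies neither quantity, so this is a range under assumptions, not a prediction. Priority is low to moderate: the analysis is secondary, small and outside the progression criteria, but the defect is in the stated analysis and cheap to remove.

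**What to change.** In section 3.1, replace the two correlation items with one sentence. Within the coaching arm, each 3-month outcome is regressed on the number of sessions completed and the participant's own baseline value of that outcome (or the partial correlation given baseline is used). The estimate is reported with its 95% CI and labelled exploratory and non-randomised. Simple change scores are not an adequate substitute, as the working shows.

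The label matters because baseline adjustment does not remove confounding by motivation or other drivers of attendance. Naming the coaching arm also settles which participants enter the analysis.

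The cost is one sentence of wording and one degree of freedom at n = 15. No new data are needed.
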